# Cost-effectiveness of 40-hour versus 100-hour vocational rehabilitation on work participation for workers on sick leave due to subacute or chronic musculoskeletal pain: study protocol for a randomized controlled trial

**DOI:** 10.1186/s13063-015-0861-4

**Published:** 2015-07-28

**Keywords:** vocational rehabilitation, subacute musculoskeletal pain, chronic musculoskeletal pain, work participation, cost-effectiveness, non-inferiority, randomized controlled trial, multicenter

## Abstract

**Background:**

Although vocational rehabilitation is a widely advocated intervention for workers on sick leave due to subacute or chronic nonspecific musculoskeletal pain, the optimal dosage of effective and cost-effective vocational rehabilitation remains unknown. The objective of this paper is to describe the design of a non-inferiority trial evaluating the effectiveness and cost-effectiveness of 40-h multidisciplinary vocational rehabilitation compared with 100-h multidisciplinary vocational rehabilitation on work participation for workers on sick leave due to subacute or chronic musculoskeletal pain.

**Methods/Design:**

A non-inferiority study design will be applied. The study population consists of workers who are on part-time or full-time sick leave due to subacute or chronic nonspecific musculoskeletal pain. Two multidisciplinary vocational rehabilitation programs following the bio-psychosocial approach will be evaluated in this study: 40-h vocational rehabilitation and 100-h vocational rehabilitation, both delivered over a maximum of 15 weeks. The 100-h vocational rehabilitation comprises five modules: work participation coordination, graded activity, cognitive behavioral therapy, group education, and relaxation. The 40-h vocational rehabilitation comprises work participation coordination and a well-reasoned choice from the other four modules. Four rehabilitation centers will participate in this study, each delivering both interventions. Patients will be randomized into one of the interventions, stratified for the duration of sick leave (<6 weeks or ≥6 weeks) and type of sick leave (part-time or full-time). The primary outcome is work participation, measured by self-reported sick leave days, and will be assessed at baseline, mid-term, discharge, and at 2, 4, 6, 8, 10, and 12 months follow-up. Secondary outcomes are work ability, disability, quality of life, and physical functioning and will be assessed at baseline, discharge, and at 6 and 12 months follow-up. Cost outcomes are absenteeism, presenteeism, healthcare usage, and travelling costs. Cost-effectiveness will be evaluated from the societal and employer perspectives.

**Discussion:**

The results obtained from this study will be useful for vocational rehabilitation practice and will provide stakeholders with relevant insights into two versions of vocational rehabilitation.

**Trial registration:**

Dutch Trial Register identifier: NTR4362 (registered 17 March 2014).

## Background

Chronic musculoskeletal pain is a major health problem associated with decreased functioning and quality of life, sick leave, and increased direct and indirect medical costs [1–4]. The majority of the costs (48 to 88 %) are attributed to indirect costs due to sick leave from work or productivity loss while at work [5, 6]. Chronic musculoskeletal pain arises when acute musculoskeletal pain does not disappear within 6 weeks, which occurs in 10–20 % of the cases [7]. After a duration of 6 weeks, it is considered subacute musculoskeletal pain (SMP), and if the pain is still present after 12 weeks, it is considered chronic musculoskeletal pain (CMP) [8]. If there is no clear medical explanation, the chronic musculoskeletal pain is called “nonspecific.”

Vocational rehabilitation is a widely advocated intervention for sick-listed workers with subacute or chronic nonspecific musculoskeletal pain [9–12]. Vocational rehabilitation is “a multiprofessional evidence-based approach that is provided in different settings, services, and activities to working-age individuals with health-related impairments, limitations, or restrictions with work functioning and whose primary aim is to optimize work participation” [13]. In addition, work participation is conceptualized as the involvement in work roles or the lived experience of work. Work participation restriction refers to problems an individual may experience at work. Examples include number of hours lost from work (that is, absenteeism), underperforming job expectations, reduced desired employment (for example, part-time employment, short-term disability, long-term disability, premature retirement, or fewer working hours than desired), and reduced career growth [14]. However, in this paper, work participation (restriction) is expressed as the number of sick leave days due to subacute or chronic musculoskeletal pain. Research shows that vocational rehabilitation improves return to work [9–12, 15–22], and thus facilitates work participation. However, the dose-effect relation of vocational rehabilitation on work participation is unclear. Several reviews on the effectiveness of vocational rehabilitation on work participation for sick-listed workers with SMP and CMP show a wide range in treatment hours [9, 11, 20, 23]. In addition, a systematic review revealed a range of 6.4 to 196.8 hours in pain rehabilitation programs [23]. So far, only one randomized controlled trial has compared the dose-effect relation of vocational rehabilitation (VR) [16]. Sick-listed workers with CMP were classified at baseline as good, medium, or poor based on their prognosis for return to work (that is, return to work defined by the authors as absence of sick pay or related benefits in a given month), and were thereafter randomized to extensive VR (approximately 120 treatment hours), light VR (approximately 20 to 30 treatment hours), or care as usual (referred back to general practitioner). After 14 months follow-up, the participants classified with poor prognosis benefited most from the extensive VR, resulting in higher return to work rates, whereas patients classified with medium prognosis benefited from both the light and extensive programs on improving return to work rates. In another paper, but using the same study construct and population as in the Haldorsen trial [16], results were obtained without the prognosis on return to work (that is, good, medium, or poor) and on a follow-up period of two years. After 2 years follow-up, the light VR resulted in the highest return to work rates compared with usual care, but significance was only found in men. Additionally, the authors found no significant difference on return to work rates between light and extensive VR or between extensive VR and usual care [24].

As resources in healthcare are scarce, it is necessary to provide stakeholders information on the cost-effectiveness of intervention programs. Economic evaluations (cost-effectiveness studies) provide information on the relative efficiency of two or more alternative interventions. The main aspects of any economic evaluation are to identify, measure, value, and compare the costs and consequences of alternatives [25]. A randomized controlled trial found that a participatory approach (approximately 40 treatment hours consisting of a workplace intervention and graded activity) for sick-listed patients with chronic back pain was cost-effective on work participation (that is, return to work) compared with usual care [18]. Similar interventions conducted in subacute low back pain patients also show promising results on cost-effectiveness [21, 24, 26, 27]. However, there are no studies known that compare the cost-effectiveness of two (or more) vocational rehabilitation programs. To provide relevant stakeholders (that is, patients, referrers, employers, vocational rehabilitation centers, healthcare insurers, and policy makers) with information about effective and cost-effective vocational rehabilitation, a comparison of two versions of vocational rehabilitation is needed.

### Objectives

The objective of this paper is to describe the design of a multicenter, randomized, non-inferiority study to evaluate the effectiveness and cost-effectiveness of 40-h vocational rehabilitation compared with 100-h vocational rehabilitation on work participation for patients with subacute or chronic musculoskeletal pain and with sick leave from work. We hypothesize that 40-h VR will be noninferior on work participation and cost-effective in comparison with 100-h VR.

The research questions are:I)For workers on sick leave due to subacute or chronic musculoskeletal pain, is 40-h vocational rehabilitation noninferior on work participation compared with 100-h vocational rehabilitation?II)For workers on sick leave due to subacute or chronic musculoskeletal pain, is 40-h vocational rehabilitation cost-effective compared with 100-h vocational rehabilitation?

## Methods/Design

### CONSORT

In the description of our study design, we follow the Consolidated Standards of Reporting Trials (CONSORT statement) with the extension of reporting on non-inferiority trials [28].

### Organization of the study

Approval for the study has been obtained by the Medical Ethics Committee of the Academic Medical Center, Amsterdam, the Netherlands (approval number: 2013_366). The trial is registered in the Dutch Trial Register (http://www.trialregister.nl/trialreg/index.asp) with identification number NTR4362. All participants will sign written informed consent forms and will be insured according to Dutch Law in case of any damage caused by participation in the study. Figure 1 shows a flow chart of the design of the study.

**Fig. 1 Fig1:**
[figure not shown]
Flow chart of the design of the study

### Study design

A multicenter, randomized, 12-month follow-up, non-inferiority study design will be performed to evaluate the effectiveness and cost-effectiveness on work participation of 40-h versus 100-h vocational rehabilitation for patients with subacute or chronic musculoskeletal pain and on sick leave from work.

### Study population

The inclusion criteria for this study are as follows: 1) individuals of working age (18 to 65 years); 2) suffering from subacute (6 to 12 weeks) or chronic (>12 weeks) nonspecific musculoskeletal pain such as back, neck, shoulder, widespread pain, Whiplash Associated Disorder (WAD I or II), or fibromyalgia; 3) having paid work (employed or self-employed) for at least 12 hours per week; 4) the expectation that the employment or self-employment will not be terminated in the year following the vocational rehabilitation program; 5) having short-term (<6 weeks) or long-term (≥6 weeks) part-time or full-time sick leave; 6) being able to understand Dutch and able to complete questionnaires in Dutch; 7) having the motivation to participate in vocational rehabilitation aimed at optimizing work participation; 8) reimbursement of program costs by the employer (that is, the work participation coordination module, see Appendix 1); 9) having an email address; and 10) having granted informed consent. The exclusion criteria for this study is having comorbidities that are the primary reason for sick leave, such as acute or specific medical problems, clinical depression or burnout, severe asthmatic symptoms, diagnosed chronic fatigue, and neuropathy.

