#### Primary outcome

The primary outcome in this study is work participation expressed as total sick leave days due to subacute or chronic musculoskeletal pain. Total sick leave days will be calculated from the start of the intervention until 12 months follow-up after discharge. Sick leave will be measured using the absenteeism items of the iMTA (institute for Medical Technology Assessment) Productivity Cost Questionnaire (iPCQ) [34]. The questionnaire has a recall period of 4 weeks and measures sick leave on working days and on a generic basis (that is, the reason for sick leave is not asked). We have made slight adaptations to measure sick leave specifically (that is, related to subacute or chronic musculoskeletal pain, or other reasons such as flu), and we have added an item to assess the working hours at this moment: “Are you working for the full number of hours you were contracted for?” This question has three possible answers: “yes,” “no, I am partly at work,” and “no, I am on 100 % sick leave.” After the answer “no, I am partly at work” the participant is asked to fill in the number of hours he/she is working per week at that moment. The iPCQ is the result of combining two existing Dutch questionnaires (PRODISQ and SF-HLQ), and is recommended by the Dutch guideline for health economic evaluations [35]. The iPCQ has been translated by a professional language institution into a patient-friendly version using more simple language, thereby increasing the feasibility and validity of the questionnaire [34]. A population with mental health problems showed a satisfactory reliability regarding the iPCQ absenteeism items (icc 0.83) [36]. Until now, reliability of the iPCQ has not been tested in our study population. This needs to be done in the near future.

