### Non-inferiority hypothesis

A reduction in sick leave days of more than 30 days per year is deemed a clinically significant improvement on work participation [15, 17–19, 24]. A difference in sick leave days of 30 or fewer (from the start of the intervention until 12-months follow-up) between 40-h and 100-h VR is assigned as the margin of non-inferiority in this study. Our hypotheses are as follows:H0: μ1 - μ2 ≥30H1: μ1 - μ2 <30

H0 is the null hypothesis, and H1 is the alternative hypothesis, μ1 is the mean number of sick leave days in the 40-h VR group, and μ2 is the mean number of sick leave days in the 100-h VR group.

Non-inferiority is claimed if the upper bound of the one-sided 95 % confidence interval of the treatment effect difference (μ1 - μ2) on work participation does not exceed 30, which means that the risk of it being inferior is within acceptable boundaries [30]. We expect a normal distribution of the primary outcome work participation. If the data on the primary outcome does not follow a normal distribution, we will perform log transformations. The margin of non-inferiority will then be interpreted as a 28 % increase in the sick leave days’ difference of μ1 - μ2. We calculated this percentage as follows:$$ 30/107 = 28\ \% $$

where 30 denotes the margin of non-inferiority and 107 the expected mean days of sick leave in the 100-h VR arm [15, 17–19, 24] during the timing of the data collection, which equals approximately 15.5 months (intervention period of 3.5 months + the follow-up period of 12 months, see Fig. 2).

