#### Effectiveness

The primary outcome work participation will be analyzed in three steps. Step 1. For every time point (that is, T0 - T8, see Fig. 2), we will present the number of sick leave days as an absolute number and as a percentage related to contract hours/month, in which the absolute number and percentages between a given time point and the preceding time point will be calculated using linear extrapolation, as recommended [36, 44, 55]. Step 2. We will calculate and present the cumulative total days of sick leave per month from the start of the intervention until the 12-month follow-up using an area under the curve for all measurement points, in which the number of sick leave days between a given time point and the preceding time point will be calculated using linear extrapolation. Step 3. Linear mixed models with multilevel analyses will be performed to assess non-inferiority between the two groups at the 12-month follow-up (that is, intervention period and 12-month follow-up) by means of 95 % confidence intervals (that is, the CI approach). To improve generalizability and comparability of this study with other studies, we will repeat step 3 at the following time intervals: I) discharge to 12-month follow-up; II) start of intervention to 6-month follow-up; III) discharge to 6-month follow-up. These additional analyses will contain no conclusions about non-inferiority and will be analyzed in the “classical” superiority manner.

A t-test or Mann–Whitney U test (in the case of no normal distribution) will be used to examine differences at discharge, at 6-month follow-up, and at 12-month follow-up (defined as the difference in outcome between baseline and last follow-up) in all secondary outcomes between the intervention groups. We will perform these analyses on superiority, thus without margins of noninferiority, as this is only relevant for the analysis of the primary outcome.

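### Outcome and margin are in unscaled working days while contracts from 12 hours a week are eligible: put contract hours in the primary model and add a contract-scaled supportive analysis

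*Protocol article*

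**What the plan says.** Under Study population, the protocol article requires "having paid work (employed or self-employed) for at least 12 hours per week". It gives no upper limit, no definition of full-time work and no expected mix of contract sizes.

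Under Primary outcome: "The primary outcome in this study is work participation expressed as total sick leave days due to subacute or chronic musculoskeletal pain". On the instrument it says: "The questionnaire has a recall period of 4 weeks and measures sick leave on working days". Items on contracted and current weekly hours are added, but no rule is given for turning partial absence into days.

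Under Non-inferiority hypothesis, the margin is 30 days over the intervention and 12 months of follow-up. It applies to a difference of arm means, where "μ1 is the mean number of sick leave days in the 40-h VR group". The planning mean in the 100-h arm is 107 days over about 15.5 months. If the data are log-transformed, the margin becomes 28 % (30/107), relative to sick leave days and not to contract hours.

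Under Effectiveness, step 1 states: "we will present the number of sick leave days as an absolute number and as a percentage related to contract hours/month". Step 2 cumulates days, and step 3 tests non-inferiority with mixed models. The percentage is not mentioned again after step 1.

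Contract hours are not among the strata under Randomization. Under Statistical methods, adjustment for baseline differences is left to be decided if a need is seen.

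**The concern.** A count of working days lost is capped by the number of days a person is contracted to work. Two patients who are both absent for the whole period can have very different totals, for a reason that has nothing to do with either program. Two things are at stake.

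- **Precision.** Spread in contract size becomes spread in the outcome. Contract hours are a known baseline source of that spread, but they are neither stratified on nor fixed in the model.
- **Interpretation.** The outcome is presented as work participation. Thirty days is a small share of a full-time worker's contracted time and a larger share of a small contract's. What the margin tolerates in proportional terms therefore depends on who enrols.

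The protocol itself treats share of contract as meaningful. It uses percentage of contract hours in the rule for extending the 40-h program and again in step 1 of the analysis. That scale does not reach the step in which non-inferiority is decided.

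**Working it through.** **The plan's own sample size.** Inputs from Sample size: margin 30, SD 80, expected difference −8, alpha 0.025 one-sided, power 80 %, loss 15 %, ICC 0.05.

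- Per arm: 2 × [80 × (1.960 + 0.842) / (30 + 8)]² = 69.6, rounded up to 70.
- If the ICC enters as a factor of 1.05 (assumed; the article does not give the factor): 70 × 1.05 / 0.85 = 86.5, rounded up to 87 per arm, 174 in total.

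This matches the stated 174 and is not in dispute. The SD and margin are in days. No SD or mean is given on a contract-hours scale.

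**Ceiling of the outcome by contract.** 15.5 months = 15.5 × 365.25 / 12 / 7 = 67.4 weeks. Maximum count = working days per week × 67.4, with no holidays deducted. The article does not state the length of a working day. Eight hours is assumed here. It fits the article's own step from 60 fewer program hours (100 − 40) to 8 working days, since 60/8 = 7.5, but that is an inference.

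| Contract | Days per week | Maximum days | 30 days as share |
|---|---|---|---|
| 40 h, 8-h days | 5 | 337 | 8.9 % |
| 36 h, 8-h days | 4.5 | 303 | 9.9 % |
| 24 h, 8-h days | 3 | 202 | 14.8 % |
| 12 h, 8-h days | 1.5 | 101 | 29.7 % |
| 12 h over 2 days | 2 | 135 | 22.3 % |
| 12 h over 3 days | 3 | 202 | 14.8 % |
| 12 h over 4 days | 4 | 270 | 11.1 % |
| 12 h over 5 days | 5 | 337 | 8.9 % |

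Relative to a 5-day worker, the share for a 12-hour contract is larger by a factor of 5/1.5 = 3.3 on 8-hour days, falling to 5/5 = 1.0 when the hours are spread over five days. Against a 36-hour week of 8-hour days the top value is 4.5/1.5 = 3.0. The same 12-hour contract thus has a ceiling anywhere from 101 to 337 days.

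**What cannot be computed.** The added variance and the trial-level meaning of 30 days both need the distribution of contract sizes, which the article does not give.

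**What a change of primary unit would do.** Suppose participants average 3.5 working days per week (assumed), SD 80 is in raw days, and all counts are rescaled uniformly to a 5-day week. The SD becomes 80 × 5/3.5 = 114.3. With the margin kept at 30 and the difference at −8, n = 2 × [114.3 × 2.802 / 38]², about 142 per arm before inflation, against 70. If the −8 is rescaled too (−11.4), n is about 120.

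**The case against.** A reader might infer that the trial tolerates up to three times the proportional loss of work. The document does not support that. The margin applies to the difference in arm means over all participants, never to one patient or contract group. The factor of about three belongs only to the smallest contracts worked in 8-hour days. A planning mean of 107 above one worker type's ceiling of 101 is not a contradiction either, because a mean can exceed one subgroup's maximum.

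A reader might also infer that the margin uses up the whole 43-day benefit cited under Methodological considerations. With an average of 3.5 days per week, 30 × 5/3.5 = 42.9. But both that average and a 5-day basis for the source trials are assumptions. At 4.5 days the figure is 33.3, and at 3 days it is 50. If the source trials had a similar contract mix and counted days the same way, 30 and 43 are like for like and nothing is lost. Reading the 43 as calendar days (43 × 5/7 = 30.7 working days) is a separate question of unit, unrelated to contract size.

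Further points for the plan:

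- Randomization balances contract size in expectation, so the arms are not biased against each other.
- Days lost is a legitimate outcome and matches the economic effect unit of one day of work participation.
- Smaller contracts shrink a difference in days, while mixed contracts widen the interval. These push the claim in opposite directions.
- The SD of 80 may already contain contract-driven variance; its unit and source population are not stated.
- The rule for partial absence may stand in the full protocol or analysis plan.

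All of this stands. It rules out a finding of bias and does not support replacing the primary outcome. It leaves untouched that contract size caps the count and is not fixed in the test.

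**Conclusion.** The point holds as one of precision and interpretation. The tested total and its margin are in unscaled working days, eligibility starts at 12 hours a week, and the contract-hours percentage stops at step 1. Attainable totals run from about 101 to 337 days, given 8-hour days for the low end and no holidays deducted. Thirty days is correspondingly 29.7 % to 8.9 % of contracted time for individual contract types. For the trial as a whole the share depends on a contract mix that is not given.

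The comparison between arms is not biased. Whether non-inferiority becomes easier or harder to claim is not known from the document.

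**What to change.** Keep total sick leave days, with the 30-day margin, as the primary outcome.

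1. Name baseline contracted hours per week as a covariate in the step 3 mixed model, fixed in advance and not dependent on an observed imbalance. In a linear model the adjusted difference is still in days, so the margin applies unchanged. Hours do not capture how they are spread over the week, so the covariate removes only part of the contract-driven variance.
2. Carry the step 1 percentage of contract hours through to a cumulative supportive analysis over the same period, and report it beside the primary result.
3. State the day unit of the 43-day, 107-day and 30-day figures: working or calendar days, and any full-time basis.

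The cost is one more covariate, one more supportive analysis and a few sentences. The steps already planned use contract hours, so no new data should be needed. Making a rescaled unit primary would cost more: on the 3.5-day assumption it would roughly double the required number per arm, and it would weight a 12-hour and a 40-hour job equally, which is a value judgement.
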